## Research Protocol:

### Creating Healthier Communities – AAMWI & OSU

- Perceived Stress Scale - The Perceived Stress Scale (PSS) is a classic 10 question stress assessment instrument to measure the perception of stress. The questions in this scale ask about your feelings and thoughts during the last month. The scale is valid and reliable.
  - Pittsburgh Sleep Quality Index - The Pittsburgh Sleep Quality Index (PSQI) is an effective instrument used to measure the quality and patterns of sleep in adults. It differentiates "poor" from "good" sleep quality by measuring seven areas (components): subjective sleep quality, sleep latency, sleep duration, habitual sleep efficiency, sleep disturbances, use of sleeping medications, and daytime dysfunction over the last month. The measure consists of 19 individual items, creating 7 components that produce one global score, and takes 5–10 minutes to complete. Cronbach's alphas range from 0.70 to 0.83, meeting the cut-point for a positive rating for within- and between-group comparisons. High correlations exist between PSQI with other measures of sleep quality (i.e., clinical diagnosis of insomnia, some variables of polysomnography and actigraphy, etc.). There is good construct validity.
  - RAND-SF 36 - The RAND Medical Outcomes Study (MOS) 36-Item Short-Form Health Survey (SF-36) [Version 1.0], consisting of 36 items included in long-form measures developed for the MOS. The SF-36 taps eight health concepts: physical functioning, bodily pain, role limitations due to physical health problems, role limitations due to personal or emotional problems, general mental health, social functioning, energy/fatigue, and general health perceptions. It also includes a single item that provides an indication of perceived change in health. It is a general measure of health-related quality of life. Reliability estimates for summary measures have exceeded 0.90. Extensive support for the construct validity of the SF-36 summary scores has also been shown and thus this measure has been included in a numerous number of clinical trials and research studies across ethnicities and populations.
- iii. Blood pressure will be checked via an automated oscillometric sphygmomanometer (Omron 5 series), weight and height, blood cholesterol, blood glucose will be assessed for each participant prior to intervention, 12 weeks (mid-point) and post intervention (24 weeks).
- iv. Blood cholesterol and blood glucose will be collected for each participant via finger stick pre-intervention, 12-weeks (midpoint) and post-intervention. The total amount of blood that will be collected for this entire research study (over 24 weeks) is less than 5 mL (less than 1 teaspoon).
- v. Waist Circumference will be measured at the umbilicus-level waist circumference will be measured using a standard tape measure with 4 oz. tension.

#### Data Management

The database used for this study is REDCap, which is a secure web-based application for building and managing data. Data will be collected prospectively by study staff using the EMR and participant report as primary sources. It is designed specifically for clinical research and administered by the Center for Clinical and Translational Research.

Permission for data access or entry will be granted or revoked at a level that is appropriate for each individual involved in the study. Following verification, data will be

## **Research Protocol: Creating Healthier Communities – AAMWI & OSU**

locked. Data and data labels can be downloaded selectively (for interim progress reports) or in entirety (end of study) directly from Redcap in SAS or Excel format. The study team will record all baseline information and scheduled visits. Study team members will collect data from participants. Surveys/questionnaires will be administered using REDCap either via a confidential internet link or using a tablet/computer at/or prior to the first session.

### **Analysis and Internal Validity**

Analytic Methods: The analytic strategy will use intent-to-treat (ITT) analysis. Preliminary analyses include descriptive statistics to check the data quality, examine variable distribution, and summarize sample characteristics. All data anomalies identified will be fully investigated and remedial strategies will be considered as appropriate.

Non-research related data previously collected at prior African American Male Wellness Walks will be used as part of this research project. We will analyze the data to evaluate longitudinal trends in the ideal cardiovascular health metrics for African American males participating in the walks.

#### **Primary outcome: Feasibility and Acceptability**

Descriptive statistics will be used to summarize quantitative data, including subject recruitment rate, retention rate, the degree of intervention adherence, and the average rating of the satisfaction of the intervention, including the content, length, and dose of the intervention. We will conduct content analyses on qualitative data obtained from verbatim transcripts of sessions and open-ended items of the battery. We will independently explore the data for patterns and significant statements that address intervention acceptability in NVivo 12 software. The research team will discuss, compare, and reduce codes iteratively until inter-coder agreement is met ( $\kappa > 80\%$ ). Finally, we will use matrices to compare qualitative and quantitative acceptability data from the questionnaires. A mixed methods approach will lead to better understanding of how the intervention is perceived, along with which/how strategies affect outcomes in patient engagement and health-related outcomes. We expect that intervention is feasible, and AA men will perceive it as acceptable; however, findings may indicate further need to adapt the intervention (e.g., length of intervention).

Secondary outcomes: 1) prevalence of participants with a primary care provider, change in social and patient activation needs; 2) Changes in cardiovascular health as per American Heart Association LS7 Metrics including blood pressure, cholesterol, glucose, smoking, body mass index, physical activity and dietary intake; and 3) prevalence of participants participating in OSU ResearchMatch. For each outcome, we will use mixed-effects linear modeling for repeated measures to (a) test the fixed effect of time, intervention group, and their interaction; (b) derive within-group and between-group contrast estimates on the change from baseline at each follow-up. Within-subject random effects will be included in the model to adjust for within-subject clustering from longitudinal follow-up. We will also adjust for potential confounders by including them as fixed-effects covariates in the model.

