### II. Background and Rationale

In 2010, the American Heart Association (AHA) published 2020 impact goals for cardiovascular health promotion with the aim of improving cardiovascular health and reducing deaths from cardiovascular disease (CVD) and stroke by 20% by the year 2020, which we have modified as shown in Figure 1 for use in the African American Male Wellness Initiative (AAMWI) walk.

| Goal/Metric       |         | Poor health                 | Intermediate health                              | Ideal health                |
|-------------------|---------|-----------------------------|--------------------------------------------------|-----------------------------|
| Current smoking   |         | Yes                         | --                                               | None                        |
| Total cholesterol |         | ≥ 240 mg/dl                 | 200-239 mg/dl or treated to goal                 | <200 mg/dl                  |
| Blood pressure    |         | SBP ≥140 or DBP ≥90 mmHg    | SBP 120-139 or DBP 80-89 mmHg or treated to goal | <120/<80 mmHg               |
| Body mass index   |         | ≥30 kg/m        | 25-29.9 kg/m                         | <25 kg/m        |
| Physical activity |         | Exercise < 3 times per week | --                                               | Exercise ≥ 3 times per week |
| Healthy diet      |         | --                          | --                                               | --                          |
| Glucose           | Fasting | ≥126 mg/dl                  | 100-125 mg/dl or treated to goal                 | <100 mg/dl                  |
|                   | Random  | ≥200 mg/dl                  | 140-199 mg/dl                                    | < 140 mg/dl                 |

Figure 1. Life's Simple 7 Goals for Cardiovascular Health (adapted for AAMWI)

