## **Research Protocol: Creating Healthier Communities – AAMWI & OSU**

individuals had diabetes. The rates of LS7 seen in this population present a tremendous opportunity and critical need for improvement. Our prior research indicates that 64% (~544 in 2017) of AA men screened at the annual AAMWI walk have either poor (0-1 ideal CVH metrics) or average (2-3 ideal CVH metrics) cardiovascular health, which places them at higher risk for diabetes, CVD and cancer. For instance, 6 out of 10 new cases of diabetes are due to not having  $\geq 4$  ideal cardiovascular health metrics. Community and provider level access and engagement to activate black men to embrace wellness and improve LS7 may lead to long-term reductions in diabetes, CVD and cancer, thus reducing disparities and improving health equity. Additionally, the lack of inclusion of AA men in clinical trials is a problem in Central Ohio and nationally that prevents the generalizability of many discoveries for the prevention and treatment of chronic diseases to AA men. Thus, there is a critical need for targeted programs to increase engagement of AA men in clinical trials.

The current efforts of the AAMWI have increased awareness of LS7 but have not led to sustained improvements in LS7 among AA men over time. For instance, from 2015-2017, ideal cardiovascular health metrics including: not smoking (ideal) decreased from 89% to 87%, ideal blood pressure decreased from 35% to 27%, ideal body mass index decreased from 22% to 19%, ideal cholesterol decreased from 81% to 69%. These sobering statistics partly reflect local and nationwide trends in AA cardiovascular health and the growing breadth of the AAMWI, which is attracting individuals from disparate areas and neighborhoods, which often have lower levels of health due to the impact of the social determinants of health. A recent analysis in Ohio, that length and quality of life for AAs in Ohio is far worse than other racial/ethnic groups and is even worse than the total population in the lowest ranked county in Ohio. These findings demonstrate the critical importance for novel targeted programming to improve LS7 and are the basis for this study.

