#### Secondary Outcomes (Pre-Post):

## Research Protocol: Creating Healthier Communities – AAMWI & OSU

- Prevalence of participants with a primary care provider
  - Change in social and patient activation needs
  - Change in cardiovascular health as per American Heart Association LS7 Metrics including blood pressure, cholesterol, glucose, smoking, body mass index, physical activity and dietary intake
  - Prevalence of participants participating in OSU ResearchMatch.
- i. We will measure feasibility via the study procedure logs (i.e., study enrollment and study contact completion).

We will assess protocol acceptability (satisfaction, usefulness, and plans and change of behavior to apply health promotion strategies). At the end of each program session, participants will complete a process evaluation via exit survey reviewed by stakeholders. We will use open-ended items to evaluate each participant's SMART goals and progress toward those goals. We will also inquire about what and how the participants like, dislike, and recommend intervention improvement. Specific questions will be: 1) What are your SMART Goals this week? 2) Do you have concerns about your ability to meet the goal(s) you set? If so, list your concern(s). 3) Have you changed your behavior as a result of the intervention? If so, how? 4) On a scale of 0 to 10 (with 0 being not at all satisfied and 10 being completely satisfied) how satisfied are you with this session? 5) On a scale of 0 to 10 (with 0 being not at all useful and 10 being most useful), how useful do you find this session? 6) What was the most useful part of this session? 7) Do you have any additional comments or suggestions?

- ii. Validated Questionnaires will be assessed prior to intervention, 12 weeks (mid-point) and post intervention (24 weeks)

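### The linear mixed model fixed for every secondary outcome also governs yes/no outcomes, where standard errors and intervals can be wrong, chiefly for ResearchMatch and for provider acquisition

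*Protocol*

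**What the plan says.** The secondary-outcomes paragraph of the Protocol (Analysis and Internal Validity) lists, among others, "prevalence of participants with a primary care provider", "prevalence of participants participating in OSU ResearchMatch" and smoking as one of the Life's Simple 7 (LS7) metrics. It then sets one rule for all of them: "For each outcome, we will use mixed-effects linear modeling for repeated measures". The model is to estimate change from baseline at each follow-up. On correlation it says only: "Within-subject random effects will be included in the model to adjust for within-subject clustering from longitudinal follow-up".

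The first two outcomes are yes/no by definition. Figure 1 in Background and Rationale gives "Current smoking" two levels, yes or none, with no intermediate class. The Protocol names no logistic model, GEE, McNemar test or robust variance. The remedial strategies it mentions concern data anomalies. Outside the model it adds only descriptive statistics, proportions among them.

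**The concern.** This is a stated rule and not a detail left for a later plan: one linear model is applied to each outcome without exception. A random-intercept linear model in its usual form pools one residual variance over the visits. The variance of a yes/no outcome moves with its prevalence. When prevalence starts near zero and rises, or when men change in one direction only, the pooled variance fits neither follow-up contrast. It is too small for the later, larger change and can be too large for the earlier, smaller one.

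ResearchMatch is the clearest case. Helping men enrol is part of the community health worker's task, and the ResearchMatch session falls in week 24, so low early and higher late registration is plausible. Provider linkage and research participation both appear among the three secondary objectives. At stake is the stated precision of those results, and the same models also carry the exploratory Wald interaction tests.

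**Working it through.** The Protocol gives no coverage, power or precision figure, so there is none to reproduce. The check compares the standard error (SE) the model would report with the true one.

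**Inputs from the Protocol.** 100 men in a single arm; 10% attrition expected, so about 90 with post-intervention data; assessments at baseline, 12 and 24 weeks. For smoking, the background says of walk attendees: "not smoking (ideal) decreased from 89% to 87" per cent, so about 13% smoked.

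**Assumptions.** All other rates; a two-sided 95% level, which the Protocol does not state; complete data; a random intercept with one residual variance.

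**Formulas.** With balanced data, this model gives the same SE to every change between visits:

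- model SE² = (mean of the three pairwise difference variances) / n
- true SE² = (that contrast's own difference variance) / n
- if a fraction d changes and nobody reverses, the difference variance is d(1 − d).

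**Worked case: ResearchMatch at 0%, 10% and 40%, no reversals, n = 100.**

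- Baseline to week 12: 0.10 × 0.90 = 0.09
- Baseline to week 24: 0.40 × 0.60 = 0.24
- Week 12 to week 24: 0.30 × 0.70 = 0.21
- Mean: (0.09 + 0.24 + 0.21) / 3 = 0.18
- Model SE, both contrasts: √(0.18/100) = 0.042
- True SE, week 12: √(0.09/100) = 0.030; ratio 0.0424/0.0300 = 1.41
- True SE, week 24: √(0.24/100) = 0.049; ratio 0.0424/0.0490 = 0.87, so 13% too small

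In 20,000 simulated trials, coverage was 99.4% at week 12 and 90.0% at week 24. About 30% of the week-12 intervals for change ran below zero, although nobody can fall below a 0% baseline.

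**Other one-directional paths (n = 100).** Ratios are from the formulas; coverage is simulated, nominal 95%.

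| Assumed path | Week-12 ratio | Week-24 ratio | Week-24 coverage |
|---|---|---|---|
| ResearchMatch 0/5/40% | 1.90 | 0.85 | about 90% |
| ResearchMatch 0/0/30% | true SE is 0 | 0.82 | about 87% |
| ResearchMatch 0/10/20% | 1.12 | 0.84 | about 88% |
| ResearchMatch 0/2/10% | 1.77 | 0.82 | about 85% |
| Provider 60/75/85% | 1.03 | 0.85 | about 90-91% |

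The week-24 shortfall appears on every path. The large week-12 excess needs registration to come mostly after week 12; at an even pace it is about 1.1. Results with 90 men are similar. With a 0% baseline, the model's interval for baseline prevalence always ran below zero.

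**Movement both ways (n = 100), week-24 coverage.** Provider 60/75/85%: 93.5%. Provider 80/90/95%: 92.3%. Smoking 13/11/9%: 94.0%. Smoking 25/20/15%: 93.6%. All are near nominal. Smoking departs clearly only if men quit and nobody starts: at 13/10/7%, coverage is 83.7% with 100 men and 89.4% with 90.

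**Two visits only.** There is then a single pair, so the mean variance is that pair's own variance. On one fitted data set the model and paired-difference SEs agreed (both 0.0492).

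**Visit-specific variance.** Estimating each contrast's variance separately brings week-24 coverage to 93-95% for ResearchMatch and provider status. At week 12 it ranges from 80% to 95% where some change occurs, and is lowest where very few men have changed.

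**The case against.** The strongest reply is that the error comes from a covariance structure the Protocol does not fix. It speaks only of within-subject random effects, and a statistical analysis plan could allow unequal variance by visit, which largely repairs week 24. That stands in part: linearity alone does not spoil the SE. But the text names neither a visit-specific nor a robust variance, and a separate variance does not cure sparse week-12 cells or keep intervals within 0-100%.

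Second, the outcome list is headed as pre-post, and the 12-week schedule covers questionnaires and biometrics without naming provider or ResearchMatch status. If these are recorded only before and after, the SE is right. The analysis text nevertheless asks for change at each follow-up, so the point is unsettled.

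A reader might infer more than the documents support:

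- **That all three yes/no outcomes get wrong coverage in both directions.** Smoking and provider status with movement both ways do not.
- **That the LS7 metrics need ordinal models.** The outcome lists name the metrics themselves and never make the poor/intermediate/ideal classes the modelled outcome. Figure 1 has no intermediate class for smoking or activity and no cut-offs for diet.
- **That the pilot's conclusions fail without this change.** Its primary outcomes, feasibility and acceptability, are summarised descriptively with qualitative analysis, and no stated decision rests on these intervals.

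**Conclusion.** The point holds in a limited form. The Protocol fixes a linear model for outcomes that are yes/no, and in its usual random-intercept form that model can misstate their precision. Under the assumed one-directional ResearchMatch and provider paths, week-24 SEs are about 13-18% too small, with coverage of about 85-91%. Week-12 SEs are about 1.4-1.9 times too large when ResearchMatch registration is concentrated late.

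This rests on three visits, one pooled residual variance, and one-directional change, with ResearchMatch near zero at baseline. Apart from the 13% smoking rate, which describes walk attendees and not the enrolled men, every rate is an assumption. The estimated change in proportion is unbiased with complete data. For secondary outcomes of a single-arm pilot, severity is minor to moderate.

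**What to change.** Replace the single rule with three.

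1. Keep the linear mixed model for continuous outcomes, such as blood pressure, cholesterol, glucose, body mass index and the Patient Activation Measure score.
2. For provider status and smoking, use binomial GEE or a logistic mixed model with clustering by participant, and report marginal risk differences. A linear model with robust or visit-specific variance is an acceptable alternative where cells are not sparse.
3. For ResearchMatch, report new registrations among men not registered at baseline, with an exact or score interval. A 0% baseline makes a logistic time effect inestimable.

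State also whether provider and ResearchMatch status are recorded at week 12. Analyses restricted to men without a provider at baseline, or to baseline smokers, are optional.

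The cost is a few sentences and some code, with no new data or visits. The downside is small numbers: if the walk's rate holds, about 13 of 100 men smoke, and a logistic model on so few may be unstable. The logistic and GEE options were not simulated here.

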### **Research Structure:**

In this single-arm pilot program, we will enroll 100 AA male participants from the annual AAMWI walk/health fair who have poor or average cardiovascular health ( $< 4$  LS7 metrics in the ideal range) with the goal of accomplishing aims exhibited in Figure 2. Our intervention involves two components: a community health worker (CHW) and peer team. Each participant will be assigned to a CHW and grouped into a team of 10 participants based on participant proximity to a central meeting location (total 10 teams). The CHW will assist in activating individual participants to engage in primary care, social support services, and enrollment in ResearchMatch. Within the teams, health coaches will assist the study team in implementing the community-based lifestyle intervention spanning LS7 principles and ResearchMatch, as shown in Figure 2 below.

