### Randomization:

This is a single-arm pilot that the study team adapted from the CDC Diabetes Prevention Program^7 and American Heart Association Check, Change, Control programs applying informed by evidence-based strategies and stakeholder feedback. Thus, participants will not be randomized and will all receive the intervention. Our study will not be randomized due to: 1) this is a pilot program that has not been previously tested for feasibility and acceptability; 2) at the time of recruitment, we will have data over 5 years showing trends in ideal cardiovascular health metrics among AAMWI walk participants for baseline comparison (not a true study comparison group); and 3) concerns from the community of participants not receiving a potentially beneficial intervention (albeit, novel and not previously tested).

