### Intervention:

The intervention is a 24-week community-based lifestyle intervention to improve cardiovascular health among AA males involving two components: a CHW and peer team. Each participant will be assigned to a CHW and grouped into a team of 10 participants based on participant proximity to a central meeting location (i.e. Columbus Recreation and Parks centers and YMCAs). Each team's four health coaches will deliver content and coaching around the lifestyle intervention described below. The intervention will be applied evenly to all participants. Health coaches will implement the curriculum [Table 1] utilizing resources from the partnering organizations. Health coaches will meet with participant teams weekly for 75 minutes. Key health coach activities include delivering education, establishing and monitoring progress in achieving individual and team-based SMART (specific, measurable, achievable, relevant, and time-bound) wellness goals.

| Weeks | Session topics                                                                                                                                                                                                                                                                                                                                                                                                                                                                                                                                                                                                                                                                                                       | Partners                   | Study Measurements                                                                       |

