## **Research Protocol:**

### **Creating Healthier Communities – AAMWI & OSU**

All statistical analyses will be performed using either SAS 9.4 or the most current version (SAS Institute, Inc., Cary, NC) or Stata 15 or the most current version (Stata Corporation, College Station, TX). Descriptive statistics (mean, median, standard deviation, proportions, etc.) of each of the collected variables will be estimated overall.

Sample Size and Power Analysis: This is a pilot study so sample size and power calculations were not performed. We will use data from this pilot study to solidify protocol parameters and estimate the degree of attrition that is considered in sample size and power calculation for a full-scale randomized controlled trial.

Missing Data: We expect missing data, for the post-intervention measures, where we expect a 10% attrition rate. We will carefully examine the pattern of the missing data and impute missing data via multiple imputation methods if missing completely at random (MCAR) mechanism is present. The mixed effects modeling approach described earlier allows for data missing at random (MAR). If the pattern of missing data indicates the potential missing not at random (MNAR), pattern-mixture modeling will be used. The robustness of findings under MCAR, MAR, and MNAR mechanisms will be evaluated.

Heterogeneity of Treatment Effect (HTE): To determine if there is HTE, we will extend our analysis models to include statistical interactions between participant factors and treatment and perform Wald tests of the interaction effect. Potential interaction factors include age, income, education level, neighborhood SES, and food insecurity. These analyses will be considered exploratory and thus no additional adjustment of p-values will be undertaken.

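### The secondary-outcome model tests an intervention-group effect and between-group contrasts that a single-arm trial cannot estimate; only within-person change over time is estimable

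*Protocol*

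**What the plan says.** The design sections of the protocol describe one arm.

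- Research Structure opens with "In this single-arm pilot program".
- Randomization states that "participants will not be randomized and will all receive the intervention".
- Intervention adds: "The intervention will be applied evenly to all participants".
- Randomization also mentions data from earlier walks, available "for baseline comparison (not a true study comparison group", and so rules them out as a control.

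The analysis text describes something else. In the secondary-outcomes paragraph of Analysis and Internal Validity, a linear mixed model for each outcome is to "test the fixed effect of time, intervention group, and their interaction; (b) derive within-group and between-group contrast estimates on the change from baseline". The paragraph on heterogeneity of treatment effect then extends these models to "include statistical interactions between participant factors and treatment and perform Wald tests of the interaction effect". It names five candidate factors (age, income, education, neighborhood socioeconomic status and food insecurity) and labels the analyses exploratory.

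**The concern.** A group effect needs at least two groups. No part of the protocol defines a second one, yet this paragraph is its only inferential model for the secondary outcomes, and the heterogeneity analysis is built on it.

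Two things are at stake. First, some of the named tests cannot be carried out, so the analyst must depart from the protocol to run anything. A separate statistical analysis plan could not repair this without contradicting the protocol, because the protocol states the terms itself. Second, there is a labelling risk. Software will usually drop the redundant terms and still print a time coefficient. Beside text that promises a group effect and heterogeneity of treatment effect, that coefficient could be reported as the effect of the intervention. A one-arm before-after comparison does not support that label.

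**Working it through.** The protocol states no power, alpha or effect-size figure on this point, so there is nothing of that kind to reproduce. The question is whether the stated terms are estimable.

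**Inputs**
- 100 participants (Research Structure).
- Three measurement times: before the intervention, week 12 and week 24 (Outcome Measures).
- One arm, all treated (Research Structure, Randomization, Intervention).
- Model terms: time, group and group by time (secondary-outcomes paragraph).

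**Main model.** Let T12 and T24 indicate the two follow-up visits, and let G indicate the intervention group. The stated fixed effects are

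b0 + b1·T12 + b2·T24 + b3·G + b4·G·T12 + b5·G·T24.

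That is 6 columns. With G = 1 for everyone this becomes

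(b0 + b3) + (b1 + b4)·T12 + (b2 + b5)·T24.

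Only three sums can be estimated. A numerical check on 100 × 3 = 300 rows gave:

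| Design | Columns | Rank | Group effect b3 | Between-group contrast at week 24, b5 | Within-group change at week 24, b2 + b5 |
|---|---|---|---|---|---|
| Single arm, as planned | 6 | 3 | not estimable | not estimable | estimable |
| Hypothetical 50/50 two-arm split | 6 | 6 | estimable | estimable | estimable |

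The two-arm row is a control. It shows that the deficiency comes from the missing comparison group and not from the form of the model. Random effects for participants do not alter the fixed-effect columns. Attrition removes rows but cannot make G vary.

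**Heterogeneity model, treatment read as arm.** One factor A adds six columns: A, A·G, A·T12, A·T24, A·G·T12 and A·G·T24. The total is 6 + 6 = 12 columns. With G = 1, A·G equals A and each A·G·T equals A·T, so the rank is 6. Factor by treatment, and factor by treatment by time, are not estimable; factor by time is. The two-arm control gave rank 12 of 12. One simulated continuous factor stood in for the five listed. Its values are an assumption and do not affect the aliasing, which holds for each factor in turn.

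**Heterogeneity model, treatment read as before versus after.** Let P = 0 at baseline and 1 afterwards, so P = T12 + T24. Then A·P = A·T12 + A·T24. This is estimable, but it is a factor-by-time term under another name. The same reading does not rescue the main model: P is a sum of the time columns, P·T12 = T12 and P·T24 = T24, so the rank stays 3.

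**After repair.** The time-only model has 3 columns and rank 3, and gives the change from baseline at weeks 12 and 24.

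**The case against.** The strongest reply is that little is lost. The sentence that names the group term also names the time effect and within-group contrasts, and both can be estimated. The secondary outcomes are headed as pre-post and largely worded as change. No power claim rests on the group term, the heterogeneity analysis is exploratory, and the protocol openly disclaims a true comparison group. All of this stands. It limits the severity, but it does not make the group terms estimable.

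Could something else fill the group term?
- *Historical walk data.* Their stated use is separate: "We will analyze the data to evaluate longitudinal trends in the ideal cardiovascular health metrics for African American males participating in the walks". No sentence enters them in the mixed model, and Randomization denies them comparator status.
- *Peer teams.* The ten teams receive the same program, so team is not an intervention group.

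A reader might infer more than the documents support:
- *That the whole secondary analysis fails.* It does not; the within-person part is sound.
- *That all five heterogeneity tests are impossible on any reading.* They fail only if treatment means arm. On the before-after reading they run, under a misleading name.
- *That the covariate sentence, "We will also adjust for potential confounders by including them as fixed-effects covariates in the model", is itself an error.* Fixed covariates are legitimate in a one-arm model, and the protocol names no post-baseline covariate. That the sentence is left over from a two-arm plan would be conjecture.
- *That selecting men with fewer than 4 ideal metrics produces a calculable spurious gain.* This is a separate matter. The protocol gives no test-retest figures. Selection happens at the walk, while labs and vitals are taken again at Week 1, so drift from screening to re-measurement is not the same as drift from a Week 1 baseline.

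**Conclusion.** The concern holds for the group effect, the group-by-time interaction and the between-group contrasts. Of the three fixed effects named, only time is estimable (rank 3 of 6), and no between-group contrast is. The factor-by-treatment tests fail if treatment means arm (rank 6 of 12 with one factor). On the alternative reading they reduce to factor-by-time terms, which show who changed more and not for whom the intervention worked better.

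This rests on the protocol's own statements that there is one arm and that everyone in it is treated alike, together with the three stated visits. It does not depend on sample size, attrition or any assumed effect. The primary outcome, feasibility and acceptability analysed descriptively, is unaffected. The text should be corrected before analysis, but the inconsistency does not undermine the pilot.

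**What to change.** In the secondary-outcomes paragraph:
- specify a one-group repeated-measures model with time as a categorical factor (baseline, week 12, week 24);
- report within-person changes from baseline with 95% confidence intervals;
- delete the group term, the group-by-time interaction and the between-group contrasts;
- describe results as change, not as a treatment effect.

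In the heterogeneity paragraph, replace factor by treatment with exploratory interactions of baseline factor and time, labelled predictors of change.

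If the historical walk data were meant as a comparator, say so, define how they enter the model, and reconcile this with the statement in Randomization.

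The cost is a few sentences and no new data. The protocol gives up only a promise of treatment-effect tests that its design cannot deliver. The repair does not require the walk screening as an extra time point. That would be an added analysis on measures that do not match: the adapted walk definitions leave diet blank, score exercise by times per week and allow random glucose, whereas the study uses its own diet and activity questionnaires.
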